**Figure 2 figure2:**
[figure not shown]
Conceptual model for TCP.

### Outcomes

The primary outcome of the intervention will be measured in self-reported point prevalence of 7-day abstinence (total abstinence from tobacco use during the 7 days preceding follow-up) at 6 months after the intervention. The secondary outcomes are self-reported point prevalence of 7-day abstinence at 12 months after the intervention and 3-month continued abstinence, daily tobacco consumption (number of cigarettes), number of quit attempts (periods of total abstinence from tobacco use for more than 24 hours) and health-related quality of life (on a scale from 0-1 where 0 represents death and 1 represents perfect health) at 6 and 12 months after the intervention. All outcomes will be based on patients' self-reports. Cost-effectiveness will be measured as the incremental cost per quality-adjusted life year.

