**Methods:**

The design is a pragmatic cluster-randomized controlled trial. The sample will consist of 928 daily tobacco users with Swedish social security numbers and permanent resident permits, recruited from 14-20 PHC centers located in socioeconomically disadvantaged areas in Stockholm County. The primary outcome will be measured in self-reported 7-day abstinence at 6 and 12 months after the intervention. The secondary outcomes will be measured in daily tobacco consumption, number of quit attempts, and health-related quality of life at 6 and 12 months after the intervention. Data will be collected through questionnaires and review of electronic medical records. Cost-effectiveness will be estimated through decision analytic modeling and measured by the incremental cost per quality-adjusted life year.

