### Study Setting and Participants

Study participants will be recruited from participating PHC centers located in socioeconomically disadvantaged areas in Stockholm County, Sweden. Eligible PHC centers will be identified based on a socioeconomic index, which takes into account the income, educational level, ethnicity and health status of the population in a PHC center’s catchment area [26]. Daily tobacco users over 18 years of age with Swedish social security numbers and permanent residence permits, fluent in one of the two most common languages in the study setting, Swedish or Arabic, will be eligible for inclusion in the study. Daily tobacco use will be defined as daily use of cigarettes, snus (smokeless tobacco) or other tobacco products for at least the last year. Ongoing treatment for tobacco cessation and cognitive impairment affecting ability to participate in the study on a voluntary basis will be applied as exclusion criteria.

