### Statistical Analysis

In order to describe the setting and the effectiveness of the randomization, descriptive statistics of the study population’s baseline characteristics at both individual and cluster level will be presented separately for the intervention and control arm, as proportions for categorical variables and as mean values with corresponding standard deviation (SD) for continuous variables.

The association between the treatment and the outcomes post-intervention will be analyzed using multiple regression models. A logistic regression model will be used for binary outcomes, including the primary outcome, 7-day abstinence. The result will be presented as an odds ratio (OR) and corresponding 95% confidence interval (CI). The association between the treatment and continuous/count outcomes, including the secondary outcomes, daily tobacco consumption, number of quit attempts and health-related quality of life, will be analyzed using multiple linear and Poisson regression models. All analyses will be conducted according to the intention to treat principle [37], meaning that the individual study participants will be analyzed according to how the PHC centers where they were recruited and treated were randomized, regardless of which intervention they received. Inference will be targeted at the individual level and hierarchical models will be used to handle potential clustering on the PHC center level. Model covariates will include age, sex, educational level, nicotine dependence, motivation and readiness to quit, previous quit attempts, previous use of pharmacotherapy, and diagnosis of chronic disease. For main analysis no missing data will be imputed. However, classical multiple imputation methods will be used for an additional sensitivity analysis if any of the included variables have more than 5% missing observations. The analyses will be conducted by the research team, including a statistician.

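### Daily tobacco consumption is counted in cigarettes, although users of snus and other tobacco are eligible and the abstinence outcomes cover all tobacco

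*Protocol article*

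**What the plan says.** All references are to the protocol article.

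- **Study Setting and Participants** sets eligibility by any tobacco product: "Daily tobacco use will be defined as daily use of cigarettes, snus (smokeless tobacco) or other tobacco products for at least the last year".
- **Outcomes** defines the primary outcome over all tobacco, as "total abstinence from tobacco use during the 7 days preceding follow-up", and quit attempts likewise, as "periods of total abstinence from tobacco use for more than 24 hours". In the same paragraph a secondary outcome at 6 and 12 months is "daily tobacco consumption (number of cigarettes", and the bracket gives its only unit.
- **Statistical Analysis** states that "daily tobacco consumption, number of quit attempts and health-related quality of life, will be analyzed using multiple linear and Poisson regression models", without assigning a model to each outcome. It adds: "All analyses will be conducted according to the intention to treat principle". No subset of participants is named for the consumption outcome. The covariate list begins "Model covariates will include age, sex, educational level, nicotine dependence, motivation and readiness to quit" and does not name tobacco product.
- **Abstract, Methods** describes the population without reference to product: "The sample will consist of 928 daily tobacco users". The abstract and Statistical Analysis both name the consumption outcome without a unit.

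**The concern.** The outcome is named for tobacco, the population uses any tobacco, and the unit counts one product. The outcomes listed beside it use the wider definition, so two outcomes in one paragraph can classify the same person in opposite ways.

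Two things are at stake. A real fall in snus or other non-cigarette use would not appear in the outcome that is meant to capture consumption. A move from cigarettes to snus would appear as a full reduction in tobacco consumption while tobacco use continues. A report on a tobacco cessation intervention could therefore describe reduced tobacco consumption that is partly product substitution.

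**Working it through.** **Step 1. The plan's own figure.** The only quantitative target is for the primary outcome (Sample Size: 7% against 14%, two-sided 5%, 80% power).

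- n per arm = [1.96·√(2 × 0.105 × 0.895) + 0.8416·√(0.07 × 0.93 + 0.14 × 0.86)]² / 0.07² = 299.9, so 300.
- Design effect on the stated inputs: 1 + (43 − 1) × 0.01 = 1.42, and 300 × 1.42 = 426.
- Attrition: 426 / 0.92 = 463.04, so 464 per arm and 928 in total.

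These match the plan. They rest on abstinence alone, so the unit of the consumption outcome does not affect them. No power figure is given for consumption.

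**Step 2. Scores under the literal unit.** The scoring below is inferred from the unit; the article does not spell it out.

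| Participant | Cigarettes/day, baseline → follow-up | Primary outcome |
|---|---|---|
| Smoker of k/day who quits all tobacco | k → 0 | abstinent |
| Smoker of k/day who switches wholly to snus | k → 0 | not abstinent |
| Snus-only user who quits all tobacco | 0 → 0 | abstinent |
| Snus-only user who halves snus use | 0 → 0 | not abstinent |
| Snus-only user who takes up cigarettes | 0 → above 0 | not abstinent |

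Rows 1 and 2 get the same consumption score and opposite primary results. Rows 3 and 4 get the same consumption score although one person quit and the other did not.

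**Step 3. Dilution.** Let s be the share using no cigarettes, equal in both arms and scored 0, and let μ₁ and μ₀ be the mean cigarettes/day among smokers in the two arms.

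- Absolute difference (linear model): (1 − s)μ₁ − (1 − s)μ₀ = (1 − s)(μ₁ − μ₀).
- Rate ratio (Poisson model): (1 − s)μ₁ / [(1 − s)μ₀] = μ₁/μ₀, which is unchanged.

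The article does not give s. For an assumed difference of 3 cigarettes/day among smokers:

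| s (assumed) | Absolute difference, all participants |
|---|---|
| 0% | 3.0 |
| 10% | 2.7 |
| 20% | 2.4 |
| 30% | 2.1 |
| 50% | 1.5 |

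**Step 4. Switching.** Suppose shares p₁ and p₀ of smokers in the two arms move from k cigarettes/day to snus and would otherwise have stayed at k. The spurious absolute difference among smokers is k(p₁ − p₀). With assumed k = 15:

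- p₁ = 10%, p₀ = 0: 15 × 0.10 = 1.5 cigarettes/day.
- p₁ = p₀ = 10%: 15 × 0 = 0.

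**The case against.** The strongest reply is that the unit is a short bracket in a condensed article. The full plan or the questionnaire might use cigarette equivalents or analyse smokers only, and no sentence says that snus-only users enter with zeros. This stands against certainty about the scoring. It does not remove the mismatch: the article states a unit, and that unit does not fit the population it enrols.

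A reader might infer more than the documents support:

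- **Snus-only users cannot change, whatever happens.** They could score above 0 by taking up cigarettes. What the unit cannot show is a reduction.
- **The treatment effect shrinks by a known percentage.** The factor (1 − s) applies to an absolute difference. With equal s it does not apply to a Poisson rate ratio, and the article leaves both models open. The value of s is not given.
- **Switching favours one arm.** This needs different switching rates. Standard Treatment says the two arms are likely to share treatment components, the prescription form being the main difference, and snus is not among the listed intervention components. Nothing suggests that switching would be one-sided, so 1.5 cigarettes/day is only an illustration.
- **Leaving product type out of the covariates biases the comparison.** In a randomized comparison that omission alone does not bias the estimate, and adding the covariate would not repair the unit.

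The reach is also limited: this is one of several secondary outcomes, and a smoker who switches to snus still counts as non-abstinent on the primary outcome.

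**Conclusion.** The point holds as a misfit between a stated unit and the enrolled population. As written, the consumption outcome cannot register reduced use of snus or other non-cigarette tobacco, and it scores a complete switch to snus as it scores quitting. Both consequences rest on taking the unit literally and on no subset being named for the analysis.

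The size cannot be fixed from the article. For an absolute difference the loss is the share s of participants who use no cigarettes. For a rate ratio with equal s there is no shrinkage. Bias from switching depends on a difference between arms that the documents give no reason to expect. The primary outcome, the quit-attempt outcome and the sample size of 928 are unaffected. The wording should be corrected, but the trial's main conclusion is not threatened.

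**What to change.** 1. Rename the outcome cigarettes per day and analyse it among baseline cigarette smokers. The baseline questionnaire is completed before the intervention, so this subset is not defined by response to treatment.
2. Report snus and other tobacco use per day among baseline users of each product, where the questionnaire collects it. Data Collection says tobacco use is recorded but does not confirm quantities by product.
3. Report by arm the proportion who switch product, so that a fall in cigarettes can be read beside any substitution.
4. Adjustment for baseline product type is optional and does not replace steps 1 to 3.

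The cost is a change of outcome wording and a few more secondary analyses. Each product-specific analysis has fewer participants, the number of secondary comparisons grows, and dual users appear in more than one analysis. Results states that recruitment is still under way, so the definition can be settled before outcomes are analysed. If product quantities are not already collected, those for participants already enrolled may be incomplete at baseline.

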### Data Collection

Data on sociodemographic characteristics, tobacco use, and nicotine dependence, previous quit attempts, self-efficacy and motivation to quit, health status and health-related quality of life will be collected through patient questionnaires. The questionnaires are based on questions from the Swedish Public Health Survey 2014 [29], a questionnaire that was used in a previous study that evaluated the effectiveness of brief advice for tobacco cessation in dental practices in Sweden [30] and the Swedish and Arabic (Lebanon) version of the EQ-5D-5L instrument [31]. Questions not included in the EQ-5D-5L questionnaire were translated from Swedish to Arabic and back by two different professional translation agencies and critically reviewed by a research assistant fluent in both Swedish and Arabic. The questionnaires were pilot tested in Swedish prior to the study start and in Arabic prior to the recruitment of Arabic speaking participants.

The measurements will be conducted at baseline (before the intervention) and 6 and 12 months after the intervention. In the follow-up questionnaires, questions regarding the tobacco cessation-related care the patients have received during the study period have been added. The baseline questionnaires will be administered by staff responsible for the treatment of patients at the participating PHC centers. The PHC providers administering the treatment will also document what treatment the patients have received (duration, content, intensity and number of visits, mode of counseling, referrals, any recommended and prescribed pharmacotherapy, follow-ups, etc) in the electronic medical records and in study specific documentation protocols. Staff will be educated in the documentation procedures before the start of the study. The follow-up questionnaires will be sent to the participants via mail by the researchers to avoid attrition caused by additional costs and administrative burden of revisits for the study participants. A reminder with a new follow-up questionnaire attached will be sent out via mail by the researchers if the follow-up questionnaire is not returned within ten days. If the reminder questionnaire is not returned, additional reminders to return the questionnaire will be sent out via mail, email and SMS text messaging (short message service, SMS) by the researchers. In connection with the second reminder, the participants will be offered the opportunity to answer the questionnaire in a telephone interview. Multiple reminders and forms of contact have been found essential in promoting high retention rates among disadvantaged research participants who are often highly mobile [32]. The strategy above is expected to be sufficient in reaching study participants who are willing to respond to the follow-up questionnaires. Arabic speaking staff will assist the researchers in contacting and collecting data from the Arabic speaking participants.

Additional data on the characteristics of participating PHC centers and providers delivering the intervention will be collected through questionnaires and interviews. This includes data on organizational aspects such as number of listed patients, number of employees, and type of professions and routines for tobacco cessation at the PHC center level and data on age, sex, profession, qualifications, and personal experiences of tobacco use and tobacco cessation at the PHC provider level. Data on structural changes in the PHC centers during the study period (eg, staff turnover) will also be collected retrospectively. This data will be collected by the researchers.

### Sample Size

The required sample size was calculated based on the primary outcome, assuming a 7% rate of 7-day prevalence in abstinence from tobacco use at 6 months follow-up in the control group, significance level of 5% and 80% power to detect a 2.0 relative risk of successful quit attempts in the intervention group compared to the control group. The estimated prevalence of abstinence in the control group corresponds to the success rate of brief advice [33] which is the minimum intervention for the control group in this study. The estimated relative risk corresponds to the relative risk of abstinence from tobacco use for combined pharmacotherapy and counseling, as recommended for the intervention group in this study, compared to minimal intervention or usual care [34]. The unadjusted sample size was found to be 300 per arm. Assuming an intra-cluster coefficient (ICC) of 0.01 according to Adams et al [35] the sample size was adjusted for design effect using the formula: 1 + (m − 1) ρ, where m represents the mean number of participants in each cluster and ρ is the ICC. Having 7 clusters per arm and 43 participants per cluster, the adjusted sample size will be 426 per arm. Finally adjusted for an attrition/drop-out of 8%, the final sample size will be 464 per arm or 928 in total. The estimated attrition rate of 8% is based on reported attrition rates from two other tobacco cessation trials with similar study designs, both conducted in the Swedish health care setting [30,36]. A higher number of participating PHC centers could decrease the required number of study participants without compromising the power to detect a statistically significant difference in the outcomes between the groups at follow-up, wherefore the aim is to recruit a total of 20 PHC centers. A total sample size of 840 would then be needed.

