### Sampling and Recruitment

PHC centers located in areas with low socioeconomic status in Stockholm County will be identified through the previously mentioned socioeconomic index [26], purposively sampled by the researchers and invited to participate in the study. The managers at the PHC centers will be contacted via telephone by the researchers and offered further information via email and a physical meeting before agreeing to participate in the study.

Study participants will be recruited by one to three appointed providers employed at each of the participating PHC centers. However, all staff at the participating PHC centers will be able to refer patients to recruiting staff for more information about the study. In order to reduce selection bias, eligible participants will be identified through a short screening questionnaire before being invited to participate. Further information about the study will be administered by the recruiting staff at the participating PHC centers and written informed consent to participate sought before invited participants will be included in the study. Staff responsible for the recruitment of study participants will receive a brief training in the study design and recruitment procedure before the study start. Recruiting staff will also receive posters to help facilitate the recruitment of individual study participants. The recruitment period is expected to last for 18 to 24 months.

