## Results

From April to November 2015, eight PHC centers were recruited and randomly assigned to the trial conditions. The PHC providers responsible for the treatment of study participants were trained in February and April 2016. Recruitment of individual study participants is currently ongoing. Recruitment of a second set of PHC centers is also ongoing. The expected study start of the second set of PHC centers is in September 2016.

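### The design effect uses the centre size before inflation (43, or 30 with 20 centres), so 928 and 840 participants give about 75% and 77% power, not 80%, before any allowance for unequal centres

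*Protocol article*

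**What the plan says.** The Sample Size section of the protocol article gives the whole calculation. It starts from "assuming a 7% rate of 7-day prevalence in abstinence from tobacco use at 6 months follow-up in the control group" and aims for "80% power to detect a 2.0 relative risk of successful quit attempts in the intervention group compared to the control group", with a 5% significance level. The result is stated plainly: "The unadjusted sample size was found to be 300 per arm". With an ICC of 0.01 this is multiplied by 1 + (m − 1) × ICC, where "m represents the mean number of participants in each cluster". For 7 clusters per arm the section takes 43 participants per cluster, reaches 426 per arm, and allows for 8% attrition to reach 464 per arm, 928 in total. It adds that 20 centres would need only 840 without loss of power. No coefficient of variation of centre size appears.

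On recruitment, the Sampling and Recruitment section says: "Study participants will be recruited by one to three appointed providers employed at each of the participating PHC centers". It states no quota or cap per centre and expects recruitment to last 18 to 24 months. The Results section reports a first set of eight centres already recruiting, and for the next set: "The expected study start of the second set of PHC centers is in September 2016".

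**The concern.** Two things in the design effect make the stated power too favourable.

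The first is the value of m. By the protocol's own definition, m is the mean number in each cluster. But 7 clusters of 43 make 301 per arm, not the 426 given in the same sentence. The 43 is the cluster size the trial would have if no inflation were needed. With the number of centres fixed, inflation has to come from larger centres, and larger centres raise the design effect again. The protocol stops after one step.

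The second is that the formula is exact only when every centre contributes the same number. Variation in size raises the design effect, so leaving it out can only flatter the power.

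At stake is how a null or borderline result would be read. A trial described as having 80% power to detect a doubling of abstinence would have about three quarters.

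**Working it through.** **Inputs, all from the Sample Size section:** 7% v 14%; 5% significance level (taken as two-sided, which reproduces the 300); 80% power; ICC 0.01; 8% attrition; 7 or 10 centres per arm.

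**Reproducing the plan.** Pooled two-proportion formula, mean rate p̄ = 0.105:

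n = [1.960 × √(2 × 0.105 × 0.895) + 0.842 × √(0.07 × 0.93 + 0.14 × 0.86)]² / 0.07² = 299.9, so 300 per arm.

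- 14 centres: design effect (DE) = 1 + 42 × 0.01 = 1.42; 300 × 1.42 = 426; 426/0.92 = 463.04, rounded up to 464 per arm, 928 in total. Agrees.
- 20 centres: m = 300/10 = 30; DE = 1.29; 300 × 1.29 = 387; 387/0.92 = 420.7, rounded up to 421 per arm, 842 in total. The protocol says 840, which is close enough to show that m = 30 was used.

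**Step 1: the centre size analysed, equal centres.** Effective n is the number analysed divided by DE. Power is Φ{[0.07 × √n_eff − 1.960 × 0.4335]/0.4307}, where 0.4335 and 0.4307 are the two square roots above.

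| Plan | Analysed per arm | m | DE | n_eff | Power |
|---|---|---|---|---|---|
| 928 / 14 centres | 0.92 × 464 = 426.9 | 426.9/7 = 61.0 | 1.600 | 266.8 | 75.2% |
| 840 / 20 centres | 0.92 × 420 = 386.4 | 386.4/10 = 38.6 | 1.376 | 280.7 | 77.3% |

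For scale, solving n = 300 × [1 + (n/k − 1) × 0.01] for k centres per arm gives n = 300 × 0.99/(1 − 3/k). That is 520 analysed per arm (about 1,130 enrolled in total) for k = 7, and 425 (about 924) for k = 10.

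**Step 2: unequal centres, CV assumed.** DE = 1 + [(1 + CV²) × m − 1] × ICC. A hierarchical model, which the protocol plans, weights centres more efficiently. For that case DE = [1 + (m − 1) × ICC] / [1 − CV² × λ(1 − λ)], with λ = m × ICC/[1 + (m − 1) × ICC].

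| CV (assumed) | 928/14, simple | 928/14, weighted | 840/20, simple | 840/20, weighted |
|---|---|---|---|---|
| 0 | 75.2% | 75.2% | 77.3% | 77.3% |
| 0.2 | 74.6% | 74.8% | 76.9% | 77.0% |
| 0.4 | 72.7% | 73.6% | 75.5% | 76.0% |
| 0.6 | 69.7% | 71.5% | 73.3% | 74.2% |

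**Step 3: separating the two causes.** If the protocol's own m is kept and only a CV of 0.4 is added, power is about 78% (928/14) and 78.5% (840/20), a loss of under 2 points. Correcting m alone costs about 5 points (80.1% to 75.2%) and just under 3 points (80.0% to 77.3%).

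**The case against.** The protocol's arithmetic is free of slips: 300, 426, 464 and 928 all follow from its inputs, and 840 is within rounding. That stands, but it does not help m, since the value used is not the mean centre size of the trial being planned.

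The objection has more force on unequal sizes. A reader might infer that one to three recruiters per centre fix the CV at about 0.41 (the values 1, 2 and 3 have mean 2 and SD 0.816), and that unequal recruitment is therefore why 80% is missed. The documents do not support this. The figure needs equal numbers of centres with one, two and three recruiters, and enrolment strictly proportional to recruiters. Neither is stated. With recruiters split 1, 2, 2, 3 the CV is already 0.35. All staff may also refer patients to the recruiters, which weakens proportionality. The later start of the second set is weak evidence too, because nothing says those centres recruit for a shorter time. Centre list size could push the CV up, but the documents do not quantify it. The hierarchical models in the Statistical Analysis section recover part of the loss.

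What remains is that unequal sizes are likely, that they can only lower power, and that their size is unknown.

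**Conclusion.** The stated 80% power is not delivered by either plan. The established cause is m: under the protocol's own rates, ICC, attrition and centre numbers, power is about 75% for 928 in 14 centres and about 77% for 840 in 20, with perfectly equal centres.

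The missing term for variable centre size is a valid secondary point, but its effect is a sensitivity range and not a finding of fact. With m corrected, an assumed CV of 0.2 to 0.6 gives about 74.6% down to 70% (14 centres) and 77% down to 73% (20 centres), or about 75% to 71.5% and 77% to 74% with efficient weighting. It would be tempting to quote the values at CV 0.4 to 0.6, about 70–73% and 73–75.5%, as the power of the trial. Those figures combine the error in m with a CV that the documents do not give, and the two parts should be kept apart.

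All figures use the normal approximation.

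**What to change.** In the Sample Size section:

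1. Compute the design effect with the centre size that the final plan analyses (about 61 for 928 in 14 centres, 38.6 for 840 in 20), giving 1.60 and 1.38.
2. Restate the power as about 75% and 77% in place of 80%.
3. Add the CV term to the formula and report the further loss over a stated range, for example 0.2 to 0.6, labelled as an assumption and shown separately from the correction of m. Say whether the simple or the weighted formula is used.

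This needs a few lines of text and no extra enrolment. The cost is a less favourable stated power.

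### The design effect assumes 43 participants per centre, but 426 per arm in 7 centres is 61 per centre, so neither stated sample size reaches 80% power

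*Protocol article*

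**What the plan says.** The Sample Size section starts from these planning values:

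- Control arm: "assuming a 7% rate of 7-day prevalence in abstinence from tobacco use at 6 months follow-up in the control group".
- Effect and power: "80% power to detect a 2.0 relative risk of successful quit attempts in the intervention group", which means 14% in the intervention arm.
- Unadjusted size: "The unadjusted sample size was found to be 300 per arm".
- Clustering: "Assuming an intra-cluster coefficient (ICC) of 0.01", with design effect 1 + (m − 1)ρ. Here m is defined as the average cluster size and ρ as the ICC.

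The section continues: "Having 7 clusters per arm and 43 participants per cluster, the adjusted sample size will be 426 per arm". An allowance of 8% for dropout then gives 464 per arm, 928 in total. It adds that more centres would reduce the number of participants needed with no loss of power, and that the aim is therefore 20 centres: "A total sample size of 840 would then be needed". The abstract carries the larger figure forward for a trial of 14 to 20 centres: "The sample will consist of 928 daily tobacco users".

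**The concern.** The product of centres per arm and participants per centre should equal the adjusted size per arm, and it does not: 7 × 43 = 301, not 426. When the number of centres is fixed, the only way to add participants is to enlarge each centre. That raises m and so raises the design effect. A design effect computed from the uninflated sample is therefore too small.

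The primary comparison is at stake, because the 80% power claim rests on this calculation at both stated designs. It also matters for conduct. The Results section reports eight centres randomised, a second set still being recruited and participant recruitment under way, so both 928 and 840 are live targets. A team that reached 20 centres could stop at 840 believing that 80% power was secured.

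**Working it through.** **Inputs, all from the Sample Size section:** p1 = 0.07; p2 = 0.14; α = 0.05; power 80%; ρ = 0.01; dropout 8%; k = 7 or 10 centres per arm. Sidedness is not stated. The two-sided test reproduces the article's figure, and the one-sided test gives 237 per arm.

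**Step 1. Reproduce the stated figures.** With p̄ = 0.105,

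n0 = [1.96·√(2p̄(1−p̄)) + 0.8416·√(p1(1−p1) + p2(1−p2))]² / (p2−p1)² = [1.96·√0.18795 + 0.8416·√0.1855]² / 0.07² = 299.9, so 300 per arm.

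- 7 centres per arm: m = 300/7 = 42.9, taken as 43; design effect = 1 + 42 × 0.01 = 1.42; 300 × 1.42 = 426; 426/0.92 = 463.04, rounded up to 464; total 928.
- 10 centres per arm: the article does not show m. Using m = 300/10 = 30 gives design effect 1.29, 387 per arm, and 387/0.92 = 420.7 per arm, or 841 in total against the stated 840.

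The 14-centre chain reproduces exactly and the 20-centre total to within about one participant, in both cases with m taken from the sample before inflation.

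**Step 2. Power at the stated sizes, with m as the article defines it.** For n analysed per arm: m = n/k, design effect = 1 + (m−1) × 0.01, effective size = n/design effect. Power is then

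Φ{[0.07·√n_eff − 1.96·√0.18795] / √0.1855}.

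| Design | Analysed per arm | m | Design effect | Effective n | Power |
|---|---|---|---|---|---|
| 14 centres, 928 | 426 | 60.9 | 1.60 | 266 | 75.2% |
| 20 centres, 840 | 420 × 0.92 = 386 | 38.6 | 1.376 | 281 | 77.3% |
| 20 centres, 928 | 464 × 0.92 = 427 | 42.7 | 1.417 | 301 | 80.2% |

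**Step 3. Size needed for 80%.** Putting m = 61 into the formula once is not enough: it gives 300 × 1.60 = 480, which raises m again. The consistent size solves n = 300·(0.99 + 0.01·n/k), that is, n = 300 × 0.99 / (1 − 3/k).

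- k = 7: n = 297/(1 − 3/7) = 519.75, so 520 analysed per arm (m = 74.3, design effect 1.73). 519.75/0.92 = 564.9 per arm, about 1,130 in total. Shortfall: 1,130 − 928 ≈ 200.
- k = 10: n = 297/(1 − 0.3) = 424.3, so 425 analysed per arm. 425/0.92 rounds up to 462 per arm, 924 in total. Shortfall: 924 − 840 = 84.

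**Step 4. Other readings of the text.**

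- If 43 really is the analysed number per centre, 7 centres hold 301 per arm, the effective size is 301/1.42 = 212 and power is 65%.
- If nobody dropped out, 464 per arm in 7 centres gives m = 66.3, design effect 1.65 and power 77.3%.
- Clusters of 43 that add up to 426 per arm need 426/43 = 9.9, or about 10 centres per arm. The stated cluster size thus fits 20 centres, not 14.

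**The case against.** The arithmetic is hard to dispute. The case on the other side is about weight and wording.

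- **The loss is modest and biases nothing.** It is about 5 points with 14 centres and 3 with 20, and no estimand or analysis changes. That stands. It is also smaller than the effect of uncertainty in the ICC. As an illustrative range (an assumption, not from the article), an ICC of 0.005 gives about 83% at both stated designs, and 0.02 gives 61% and 67%. But the article fixes the ICC at 0.01 and claims 80% on that basis, and at that value the claim fails.
- **The principle that more centres need fewer participants is right.** It is: 1,130 falls to 924. Power at 20 centres with 840 is even slightly above that at 14 with 928. What is wrong is the number 840 as a size that delivers 80%.
- **Covariate adjustment and pairing of centres might recover some power.** The stated calculation takes no credit for either. It also ignores unequal cluster sizes and the small number of clusters, which work the other way. A t reference on 12 or 18 degrees of freedom would give about 68% for 14 centres with 928 and 73% for 20 with 840. The article does not specify that reference, so the finding does not rest on it. On the same reference, 20 centres with 928 would give about 76%.
- **The value m = 30 for 20 centres is inferred.** True, but the shortfall at 840 follows from the article's inputs however 840 was obtained.

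**Conclusion.** The concern holds. The sample size paragraph contradicts itself, and the 80% power claim is not met at either stated design: about 75% for 14 centres with 928 participants and about 77% for 20 centres with 840. The totals are about 200 and 84 short of what 80% requires. These figures use the article's own planning rates, ICC, dropout and normal approximation, with a two-sided test and equal cluster sizes. Nothing elsewhere in the article corrects the paragraph. The error should be corrected because it concerns the primary outcome and offers a reduction to 840 that the inputs do not support.

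**What to change.** Rewrite the Sample Size paragraph as follows:

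- Define m as analysed participants per centre at the final sample size, and solve for n and m together.
- Restate power as about 75% for 14 centres with 928 and about 77% for 20 centres with 840.
- Withdraw 840 as sufficient with 20 centres. The general remark about more centres can stay.
- Keep 928 as the target and tie it to the 20 centres already aimed for (m = 42.7, design effect 1.42, power 80%).
- Because the design allows 14 to 20 centres, say what 928 delivers if fewer join: by the same formula, about 75% with 14, 77% with 16 and 79% with 18. Give about 1,130 as the size for 80% with 14.
- In the abstract, link 928 to 20 centres.

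The cost is a corrected paragraph and a less favourable stated power if only 14 centres take part. The 928 target does not change.
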